## Abstract

**Background::**

Alcohol dependence is one of the biggest problems facing public health worldwide. Currently, it is an under-diagnosed and under-treated disease. Even when given treatments for addiction withdrawal, over 2/3 of patients who have undergone abstinence-oriented treatment will relapse in the first year. Therefore, it is necessary to find an efficacious way to prevent and treat alcohol dependence. ASF (a Compound of Traditional Chinese Medicine) has proven to inhibit the formation and expression of ethanol-induced behavioral sensitization and the development of conditioned place preference in mice. As an empirical prescription for abstinence from alcohol, ASF has long been used in clinical patients. However, the effect of ASF in humans has not yet been investigated. The purpose of this study is to evaluate the efficacy of ASF for patients with alcohol dependence.

**Methods::**

The effect of ASF will be studied in a randomized, double-blinded, placebo-controlled clinical trial. 82 outpatients and inpatients will be recruited and randomly assigned to treatment with either ASF or placebo for 6 weeks as a complement to cognitive behavioural therapy. The primary endpoints are the changes in the average daily alcohol consumption of the 2 groups before and after treatment and comparison of the scores of the psychological craving self-rating scale during the courses of treatment of 2 groups. The secondary endpoints include abstinence rates of the 2 groups during the follow-up period, days without consumption, and changes of Short Form Health Survey (SF-36) scores in 2 groups before and after therapy.

**Discussion::**

This study is the first randomized controlled trial to investigate ASF in the treatment of alcohol dependence. ASF is likely to be a new and effective drug for the treatment of alcohol dependence developed from natural products with a low incidence of side effects or toxicity.

**Trial Registration::**

Registry number: ChiCTR2000039397.

## Introduction

1

Harmful drinking has been listed by the World Health Organization as the fifth leading risk factor for premature death and disability worldwide, and it is also the main cause of death and disability in developing countries.^[1]^ Alcohol dependence is one of the biggest problems facing public health worldwide. Now, it is an under-diagnosed and under-treated disease, over 2/3 of patients who have undergone abstinence-oriented treatment will relapse in the first year.^[2]^ The pathogenesis of alcohol dependence is closely related to the dysfunction of the reward pathway in the brain. The reward effect of alcohol is mainly transmitted by the “reward pathway” composed of midbrain limbic dopamine neurons and inhibitory gamma aminobutyric acid (GABA) nerve fibers. Normally, a variety of neurotransmitters, including glutamate, GABA, serotonin, glycine, and hypothalamic neurohormones, can regulate inhibitory GABA nerve fibers to maintain the excitability of the midbrain limbic dopamine system.^[3]^ When drinking, alcohol first acts on specific targets, including N-methyl-d-aspartate (NMDA), GABA, glycine, opioid, serotonin, and nicotinic acetylcholine receptors (nAChRs). Then, through the corresponding neurotransmitter or neuropeptide system, alcohol weakens the inhibitory level of dopaminergic pathway in the midbrain margin and increases the level of dopamine release in nucleus accumbens (NAC). Due to alcohol abuse, high-frequency alcohol stimulation can adapt to the structure of reward pathway, leading to dysfunction of the latter and inducing alcohol dependence.^[4]^ How to effectively prevent and treat alcohol dependence caused by excessive drinking has become a studied hot issue in the world. Alcohol dependence is treated with cognitive behavioral therapy (CBT) and pharmacologic treatment.^[5]^ The underlying neuroanatomical underpinnings of alcohol addiction and the therapeutic effect of CBT have not yet been established, although functional MRI research has begun to clarify the neural basis of alcohol dependence. There is a lack of unified and effective drugs for the treatment of alcohol dependence. Three drugs are currently approved by the US Food and drug Administration for the treatment of alcohol dependence, namely, disulfiram, naltrexone, and acamprosate. These drugs can reduce alcohol intake in some patients; however, serious side effects such as related central nervous system symptoms and poor tolerance limit their application range.^[6]^ In view of the low abstinence rate and high recurrence rate of these prescription drugs, there is an urgent need for new and more effective drugs of alcohol dependence. The main driving force for re-drinking after withdrawal treatment is psychological craving. Therefore, reducing the craving for drinking is the key to preventing relapse and treating alcohol dependence. Natural preparations developed from natural products with a low incidence of side effects or toxicity will likely be used to treat alcohol dependence, prevent, and reduce the recurrence. The high-efficiency drugs developed from natural products also show broad market prospects.^[7,8]^

Under the condition of acute short-term drinking, the level of dopamine (DA) in NAC increased rapidly, which is mainly in the positive reinforcing effects of alcohol; while chronic and long-term drinking could cause structural remodeling and down-regulation of reward pathways, mainly showing negative reinforcement of alcohol.^[4]^ Alcohol can inhibit the function of excitatory glutamate receptors and decrease excitatory effect on inhibitory GABA nerve fibers, thereby causing the de-inhibition of dopaminergic neurons in VTA and the increase of DA levels in NAC. That is to say, repeated drinking increases the release of dopamine transmitter in reward pathway, arouses the pleasure of drinkers and produces drinking cravings, which are the positive reinforcement effects of the reward system. Anxiety and other symptoms caused by withdrawal produce craving for drinking, which is in the negative reinforcing effects of reward system, leading to compulsive drinking behaviors.^[9,10]^ Both of them act on the motivation system successively, causing addictive behaviors. ^[11]^ The ideal drugs can reduce alcohol craving by safely and effectively controlling the positive and negative reinforcement effects of alcohol, so as to treat alcohol dependence.

A Compound of Traditional Chinese Medicine (ASF) used in this study comes from the hangover recipe of [name]. ASF is a compound preparation of traditional Chinese medicine made from Semen Ziziphi Spinosae and Epimedium. Icariin (ICA), the active component of Epimedium, is a flavonoid compound extracted from plants of the genus Epimedium. ICA can regulate the metabolic balance of excitatory amino acid and inhibitory amino acid transmitters by increasing GABA content, decreasing glutamate (Glu) and glutamine content, and reducing Glu/GABA ratio.^[12]^ And total flavone of herba epimediumon (TFE) can increase the release of GABA in the periventricular system of rats and increase the affinity of GABA to the receptor GABAA.^[13]^ Jujuboside A, the active component of Semen Ziziphi Spinosae, increases the expression of GABAA receptors through the blood–brain barrier.^[14]^ The alcohol extract of Semen Ziziphi Spinosae can significantly reduce the expression of N-methyl-d-aspartate receptor 1 and enhance the expression of CABAA receptor 1 in the brain of mice with yin deficiency.^[15]^ The total saponins of Semen Ziziphi Spinosae can reduce the excitatory neurotoxicity in the brain by down-regulating the ratio of Glu and GABA, 2 amino acid neurotransmitters in the old rat model.^[16]^

At present, a variety of drugs for the treatment of alcohol dependence can inhibit the reward effect caused by alcohol and regulate the activity of the reward pathway by acting on GABA receptors at the same time, which has become an important idea of the development of drugs for the treatment of alcohol dependence. Reducing the craving for drinking is the key to preventing relapse and treating alcohol dependence. In view of the fact that both active ingredients can increase the expression of GABAA receptors, whether can we guess Chinese medicine compound ASF by enhancing the inhibition of GABA nerve fibers on the dopamine system in the midbrain limbic region reduce the level of dopamine in NAC caused by alcohol, lower the level of reward effect, and reduce alcohol craving, thereby playing a role in getting rid of alcohol dependence. In China, the application of traditional Chinese medicine has a long history in the prevention and treatment of alcoholism and anti-inebriation.^[17]^ Clinically, ASF has a good therapeutic effect on patients with alcohol addiction. Therefore, in order to verify the efficacy of ASF on patients with alcohol dependence, and to evaluate whether ASF can reduce alcohol craving as its mechanism of action. We have designed a 6-week clinical trial including 82 patients with alcohol dependence. Six weeks are sufficient for the pilot protocol because it is intended to assess the efficacy and tolerability of ASF in the treatment of alcohol-dependent patients.

## Methods/design

2

### Design

2.1

The study is a 6-week randomized, controlled, prospective, double-blind clinical trial. After obtaining informed consent, the 82 alcohol-dependent patients recruited will be randomly divided into the ASF group and the placebo group according to 1:1. The study will include a 6-week treatment period and a 12-week follow up time. Both groups of patients will receive psychosocial alcohol therapy and some conventional symptomatic treatments such as liver protection. Besides, for those with severe abstinence symptoms during abstinence, benzodiazepines can be given as appropriate. On this basis, patients in the ASF group will be treated with 1 dose of ASF 3 times a day, while the control group will receive placebo treatment. The purpose is to evaluate the efficacy and tolerability of ASF in treating patients with alcohol dependence and explore the action mechanism of ASF. The protocol is presented in line with the Standard Protocol Items: Recommendations for Interventional Trials 2013 statement (the SPIRIT figure for the schedule of enrollment, interventions, and assessments is presented in Fig. 1; the checklist of SPIRIT is in Supplemental file 1). The diagram of the study flow is shown in Figure 2.

**Figure 1 F1:**
[figure not shown]
SPIRIT figure: Schedule of enrollments, interventions, and assessments: [1] TLFB = Timeline Follow-back method; [2] AUDIT = Alcohol Use Disorders Identification Test; [3] ICD-10 = International Classification of Diseases, 10th Edition; [4] Serum γ-GT = serum γ-glutamyl transpeptidase; [5] SF-36 = Short Form Health Survey; [6] PACS = Pennsylvania Alcohol Craving Scale; [7] CIWA-Ar = Clinical Institute Withdrawal Assessment of Alcohol Scale, Revised; [8] MAST = Michigan Alcoholism Screening Test; [9] COMBINE SAFTEE = COMBINE Systematic Assessment For Treatment Emergent Events; [10] Safety assessment = blood routine examination, stool routine examination, urine routine examination, kidney function test, liver function test, electrocardiography; [11] SCL-92 = Symptom Checklist; [12] DUDIT = Drug Use Disorders Identification Test.

**Figure 2 F2:**
[figure not shown]
Diagram of the study flow.

### Ethics approval

2.2

The study protocol was consistent with the Declaration of Helsinki (Edinburgh 2000) and has been registered in the Chinese Clinical Trial Registry (registration number: ChiCTR2000039397). The protocol was approved by the Medical Ethics Committee of Affiliated Hospital of Chengdu University of Traditional Chinese Medicine (Approval No: 2020SL-011). The design and implementation of the protocol were tracked by the members of the Ethics Committee. All the modifications to the study protocol, CRF, informed consent form, and others will be approved by the Ethics Committee. All the modifications will be updated on the Chinese Clinical Trial Registry.

### Recruitment

2.3

The patients will be recruited from the outpatient or inpatient department of the Affiliated Hospital of Chengdu University of Traditional Chinese Medicine. The clinicians participating in the withdrawal treatment unit will conduct preliminary screening of patients in the inpatient or outpatient department, and briefly describe the study to the patients who meet the criteria. If the patients are interested in participating, the clinician will alert the research team. A member of the research team will provide them with a comprehensive oral and written description of the research's aims and procedures and the research team members will understand their rights and responsibilities while participating in the study. Screening examinations only be performed after they have agreed to participate and signed the informed consent form. During screening, the patients will undergo related examinations to make sure that all inclusion criteria and none of the exclusion criteria are met.

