### Treatment plan

3.1

All patients will receive psychosocial alcohol treatment based on psychological education elements, motivational interviews, and cognitive behavioral therapy, including informing patients about the causes and consequences of alcohol dependence, the necessity of treatment, and how to conduct the treatment of alcohol abstinence. At the same time, family members should be educated about compliance with the treatment plans. Regular psychosocial alcohol treatment was given to abstainers once a week for 6 weeks. According to the abnormal blood chemical features of the patients, the patients will be selectively given corresponding treatment measures such as liver and kidney preservation, correction of electrolyte and acid–base disturbance, effective fluid infusion, vitamin supplementation, etc. The patients with severe withdrawal symptoms during abstinence could be treated with benzodiazepines.

Patients will be randomly assigned to receive ASF or placebo in a ratio of 1:1.

Experimental group (ASF group): On the basis of basic treatment, the patients will take 10 g ASF 3 times daily, dissolved in 150 mL of warm boiling water, for 6 weeks.

ASF used in this test is provided by the pharmaceutical Department of Affiliated Hospital of Chengdu University of Traditional Chinese Medicine (Sichuan, China).

The whole ingredients of ASF are Epimedium 15 g, Semen Ziziphi Spinosae 15 g. One dose every day, 10 g each time, 3 times a day. The herbs in ASF are mixed, processed, filtered, and spray-dried by pressure to form granules, and packaged into single-dose pouches, each weighing 10 g.

Control group: In addition to the basic treatment, the participants will take placebo granules of 10 g each time, 3 times a day. The placebo granules were dissolved in 150 mL of warm boiling water, for 6 weeks.

The placebos in the study are composed of starch and have no active ingredients.

By adding various food pigments, the appearance and taste of the placebo are as close to the real granules as possible.

The drug distribution of the study will be performed by a pharmacist who is not involved in clinical management to preserve the double-blind design. Each time the patient takes the medication, the research nurse will supervise the process and count the number of medication bags taken and not taken.

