### Outcome measures

3.2

Primary outcomes: The primary outcomes are the changes in the average daily alcohol consumption of the 2 groups before and after treatment and comparison of the scores of the psychological craving self-rating scale during the courses of treatment of 2 groups.

Secondary outcomes: The secondary outcomes include abstinence rates of the 2 groups during the follow-up period, days without consumption, and changes of Short Form Health Survey (SF-36) scores in 2 groups before and after therapy.

The researchers will use weekly self-reports during the follow-up period, clinicians’ judgments, and biochemical examinations to determine whether the patient is abstinent. If the patient has drunk no more than 1 cup since the last visit, the GGT level is normal, or has not increased since the last examination, and the respiratory alcohol concentration is less than 0.10 g/L, the patient is judged to abstain from alcohol.

From the first week to the sixth week, vital signs will be monitored daily. The physical examination will be carried out weekly. The respiratory alcohol concentration will be measured once a week, and drinking craving and adverse events will be evaluated weekly at the time of enrollment and at weeks 2, 4, 6, and 7, serum γ-glutamyl transpeptidase (γ-GT) and blood alcohol concentration will be detected. At weeks 0, 3, and 6, the doctors will give the patients electrocardiograms, and urine pregnancy, blood routine and blood biochemical levels will be detected. During the follow-up period, serum γ-GT and respiratory alcohol concentration will be measured once a week.

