### Questionnaires

3.3

At week 0 and week 6, as well as during the follow-up period, the examiner will work closely with the patient to fill in this Timeline Follow Back (TLFB) schedule for the past month, based on the alcohol diary collected weekly. The TLFB has been widely evaluated and tested,^[19]^ and in previous studies,^[20]^ it has been proved to have high retest reliability. The data collected by TLFB will be applied to evaluate the effects on the primary outcomes and secondary outcomes.

Baseline data for the Clinical trial, the Alcohol Use Disorders Identification Test (AUDIT) questionnaire, the TLFB interview, and the diagnostic instruments or questionnaires for diagnosis of alcohol addiction will be collected routinely for all patients. At week 0 and week 6, as well as during the follow-up period, the questionnaires will be conducted including: demographics (age, gender, marital status, occupation), alcohol consumption (TLFB), withdrawal symptoms (CIWA-Ar), alcohol addiction (MAST), craving (Pennsylvania Alcohol Craving Scale (PACS)), drinking behaviors (AUDIT), health status (SF-36), psychopathology (Symptom Checklist (SCL-92)),drug use (DUDIT), and adverse events (COMBINE Systematic Assessment For Treatment Emergent Events (COMBINE SAFTEE)).

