### Compliance

3.5

During the treatment phase, the researchers will record the type, frequency, and dose of any drug received by the patient during the hospitalization, monitor the patient's medication compliance ((drug bags distributed-returned bags)/total number of prescription bags) and other medications taken during the treatment period, and copy any relevant clinical records made at the time of admission. Another researcher who does not participate in the training management and is blinded to the treatment allocation of the patients will contact follow-up interviews including abstinence and TLFB, during the follow-up period after treatment. According to the intention-to-treat principles, patients who withdraw from treatment will still be contacted by researchers for follow-up before completing the 6 weeks of treatment, unless they withdraw from the study.

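### Inpatients and outpatients are pooled, and any ward days in the week-6 drinking window count as days at home, which costs the consumption outcome sensitivity and precision

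*Protocol article*

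**What the plan says.** **Population.** The Methods paragraph of the abstract states that "82 outpatients and inpatients will be recruited and randomly assigned to treatment", and section 2.3 (Recruitment) repeats both sources: "The patients will be recruited from the outpatient or inpatient department". No split between settings is given.

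**Outcome.** Section 3.2 (Outcome measures) names two primary outcomes. The first is "changes in the average daily alcohol consumption of the 2 groups before and after treatment"; the second is craving. The number of alcohol-free days is a secondary outcome.

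**Window.** Section 3.3 (Questionnaires) has the examiner, at week 0, at week 6 and during follow-up, "fill in this Timeline Follow Back (TLFB) schedule for the past month, based on the alcohol diary collected weekly". It says these data serve the primary and secondary outcomes. Section 2.1 (Design) sets the timeline: "The study will include a 6-week treatment period and a 12-week follow up time".

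**Hospital stay.** Section 3.5 (Compliance) has researchers record, in the treatment phase, "the type, frequency, and dose of any drug received by the patient during the hospitalization", and copy clinical records made at admission. No section states how long inpatients stay, whether they have leave, or how hospital days enter the drinking measures.

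**Allocation and analysis.** Section 2.5 describes SAS random numbers in envelopes opened in order of entry, 41 per arm, with no setting stratum. Section 3.8 compares continuous variables between groups with an independent-sample t test and mentions no setting or baseline term for consumption.

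**The concern.** A day on a withdrawal ward offers much less opportunity to drink than a day at home, whichever treatment is taken. If such days fall in the week-6 month, they lower measured consumption in both arms and leave less room for ASF to show a difference. Setting then also becomes a strong predictor of the outcome that the stated methods ignore.

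Two things are at stake. A weak or null result on the first-named primary outcome would be harder to interpret, because lack of effect and lack of opportunity to drink both push the arms together. The estimate would also be noisier than it needs to be, because the inpatient share can differ between arms by chance. If hospital days are not recorded on the calendar during the trial, the question may not be answerable afterwards.

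**Working it through.** **The plan's own figure.** Section 2.4 gives 34 per arm for 54.5% versus 16.7%, alpha 5%, power 90%. The two-sided pooled formula gives

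n = [1.960·√(2·0.356·0.644) + 1.282·√(0.545·0.455 + 0.167·0.833)]² / 0.378² = 31.6, so 32 per arm.

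This is within 2 patients of the stated 34, and 68 × 1.20 = 81.6 gives the stated 82. The calculation is for a binary rate. The protocol states no power for consumption, so the 90% used below is an illustrative starting point.

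**Where the window falls.** Treatment lasts 42 days. A past-month calendar completed at week 6 reaches back 28 to 31 days, to about day 11 to day 14. The whole window lies inside treatment.

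**What a ward day does.** Take a patient with pre-treatment intake B who is on the ward for the whole window and does not drink. The change is 0 − B = −B in either arm, so this patient carries no information on the drug.

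**Dilution.** Let f be the share of patients confined for the whole window (assumed; the documents give none), with the same share in each arm. The expected arm difference is (1 − f) times the difference among the others. With the SD unchanged,

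power = Φ[(1 − f)(1.960 + 1.282) − 1.960], where the z values sum to 3.2415 before rounding.

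| f | (1 − f) × 3.2415 | minus 1.960 | power |
|---|---|---|---|
| 0 | 3.242 | 1.282 | 90% |
| 10% | 2.917 | 0.957 | 83% |
| 25% | 2.431 | 0.471 | 68% |
| 50% | 1.621 | −0.339 | 37% |

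With 34 evaluable per arm, the 90% row corresponds to a standardised difference of 3.2415 × √(2/34) = 0.786. To regain 90%, n per arm would be 34/(1 − f)²: 42, 61 and 136.

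**Partial stays.** If inpatients spend only a share w of the window on the ward, and the effect accrues evenly over days, f is replaced by f × w. Half the patients hospitalised for half the window gives 0.50 × 0.50 = 25%, hence about 68%. Short stays that end before about day 11 give no dilution at all.

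**Chance imbalance.** Suppose 35 of the 82 are inpatients (assumed). With 41 per arm and no stratification, the hypergeometric distribution gives about a 37% chance that the arms differ by 5 or more inpatients. A 15 versus 20 split is a gap of 5/41 = 12.2 percentage points. If all of them were confined throughout, mean on-treatment intake would differ by about 12% of outpatient intake with no drug effect.

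**The case against.** **Confinement is inferred.** A reader might conclude that, for inpatients, the outcome measures confinement and not ASF. The documents do not support that. No section says that inpatients stay for six weeks or for the calendar month, or that they cannot drink. Section 3.1 says "Each time the patient takes the medication, the research nurse will supervise the process" and section 3.2 has daily vital signs, but both are written for all patients, outpatients included, so they do not mark a ward stay. Weekly diaries, weekly breath alcohol and a count of returned bags suit patients who can drink and hold their own supply. Only section 3.5 points to a stay, and it gives no length. This objection stands and limits the claim to whatever hospital time falls in the window.

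**Randomisation protects the comparison.** Ward stays present at entry fall on both arms alike in expectation. Chance imbalance is part of the variation the t test allows for, so type I error is not inflated. This stands too: the cost is power and precision.

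**A condensed article may omit detail.** The full protocol may define the window or stratify the list, and the article does not say outright that the week-6 calendar alone supplies the after value. Silence on these details would not be a fault in itself. But the article does describe the randomisation and the test, and neither uses setting.

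**Other outcomes remain.** Craving is the second primary outcome, and drinking is followed for 12 weeks after treatment. A null consumption result would not stand alone, so a claim that the trial becomes uninterpretable goes too far.

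**Conclusion.** The point holds in a limited form and is of moderate weight. Two settings with different opportunity to drink are pooled, the week-6 drinking window lies inside treatment, and the stated methods treat hospital days like days at home and leave setting out of allocation and analysis.

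The size depends on two figures the documents do not give: the inpatient share and the time on the ward within the window. Under full confinement, an unchanged SD and a nominal 90% power, power would be about 83%, 68% or 37% at shares of 10%, 25% or 50%. With shorter stays the loss is smaller and can be nil.

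This is a loss of sensitivity and precision on consumption and on alcohol-free days. It is not a systematic bias in favour of ASF, and it does not apply in the same way to craving or to drinking in follow-up.

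**What to change.** 1. Stratify the SAS randomisation list by inpatient or outpatient status at entry (section 2.5).
2. Analyse consumption with a model that includes setting at entry and baseline consumption, in place of the unadjusted t test (section 3.8). This removes the noise due to setting; it does not restore a difference already diluted by ward days, hence steps 3 and 4.
3. Code hospital days on the existing drinking calendar, and report consumption over days outside hospital as a sensitivity analysis. It should not be the primary analysis: hospital days arise after randomisation, and conditioning on them could bias the comparison if treatment affects discharge or readmission.
4. Report follow-up consumption, already collected, for all patients in both settings as a supportive analysis. Do not substitute follow-up values for inpatients only, because that would mix an on-treatment and a post-treatment quantity in one endpoint.

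The cost is two randomisation lists instead of one, one extra code on the calendar and slightly more analysis. No extra visits or patients are needed. Step 1 has to be in place before the first patient is randomised.
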